#### Aim 1: effects of teacher training program on students

Grounded in SDT and CMC, the first aim of this study will be to assess the impact of a teacher training program aimed at enhancing relatedness-supportive behaviors and class cohesion while minimizing relatedness-thwarting behaviors on students’ affective, behavioral, and cognitive outcomes. In line with this aim, three hypotheses will be tested. It is hypothesized that, by Time 2 (T2), experimental group students will perceive improvements in their PE teachers’ relatedness-supportive behaviors (Hypothesis 1), class cohesion, relatedness satisfaction, autonomous motivation, and affective (i.e., problematic relationships), behavioral (i.e., group processing), and cognitive variables (i.e., learning and academic performance; Hypothesis 2) compared to baseline values (Time 1 [T1]) and control group students. Given the lack of previous studies, no specific hypotheses will be formulated regarding the intervention’s long-term effects (Time 3 [T3]) on the study variables. Finally, students’ relatedness satisfaction/frustration and class cohesion, representing an individual-level and a group-level factor, respectively, will serve as mediators in the indirect relationship between the independent variable (i.e., treatment condition) and affective, behavioral, and cognitive outcomes, specifically in autonomous motivation, problematic relationships, group processing, learning, and academic performance (Hypothesis 3, see Figure 2).

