### Plan of analysis

A mixed-method analysis will be conducted to evaluate the training program, as well as to assess the impact of its implementation in PE lessons on the study variables for both teachers and students. Regarding the quantitative analysis, first, a descriptive analysis will be conducted to evaluate both teachers’ and the external researcher’s perceptions of the training program, assessing aspects such as its innovation, practical relevance, and the feasibility of the strategies implemented. Second, to assess the impact of the intervention program on the study variables for both teachers and students, the nature of the variables will first be examined through tests of normality, validity, and reliability across the three measurements. Third, the assumptions of independence, linearity, and homogeneity of variance will be verified to ensure the appropriateness of analyses based on the general linear model. Fourth, between-group and within-group differences will be analyzed using repeated-measures multivariate analysis of covariance (MANCOVA). A 3 × 2 (Time × Condition) repeated measures MANCOVA will be performed for both teachers and students, with covariates such as age, sex, teaching experience, type of school, and school location for teachers, and age, sex, sociocultural background, and school grade for students. If parametric assumptions are not met, appropriate non-parametric alternatives such as the Wilcoxon signed-rank test (for within-group comparisons) and the Mann–Whitney U test (for between-group comparisons) will be used. Subsequently, to examine intragender differences of the intervention on study variables, a 3 × 2 × 2 (Time x Condition x Sex) repeated measures MANCOVA will be performed for both teachers and students. To further examine changes in each outcome variable over time (T1, T2, and T3) within each group (experimental vs. control), multiple paired t-tests with Bonferroni correction will be conducted. Effect sizes will be calculated using partial eta squared (*η^2^ₚ*). Effect size thresholds will be interpreted as small (*η^2^ₚ* > 0.01), moderate (*η^2^ₚ* > 0.06), or large (*η^2^ₚ* > 0.14) following Cohen’s criteria. For all analyses, the significance threshold will be set at *p* < 0.05. All statistical analyses will be conducted using IBM SPSS Statistics v.25.0. Finally, a longitudinal structural equation model will be employed through the statistical software Mplus (Muthén and Muthén, 1998-2019) to analyze the predictive relationships between the study variables, allowing for the observation of potential differences at the three specific times (T1, T2, and T3) when data are collected.

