In line with these contributions, the effectiveness of the intervention will be examined through a series of research hypotheses. According to Hypothesis 1, students in the experimental group are expected to show greater improvements in their perception of relatedness support and relatedness thwarting from their PE teacher compared to baseline values and the control group students at post-test (T2). Similarly, it is anticipated that experimental group students will show greater improvements in class cohesion, motivational variables (i.e., relatedness satisfaction/frustration and autonomous motivation), and affective (i.e., problematic relationships), behavioral (i.e., group processing), and cognitive variables (i.e., learning and academic performance) compared to baseline values and control group students (Hypothesis 2).

Additionally, it is expected that students’ relatedness satisfaction/frustration and class cohesion will mediate the effect of the program on affective, behavioral, and cognitive outcomes (Hypothesis 3). All these expected outcomes from the first three hypotheses are supported by scientific literature, as correlational evidence suggests that students’ perceptions of relatedness-supportive behaviors are associated with positive outcomes in PE (Leo et al., 2023e; Sparks et al., 2017; Vasconcellos et al., 2020), while relatedness-thwarting behaviors are linked with maladaptive outcomes (Leo et al., 2023e). Similarly, class cohesion (both task and social cohesion) has been positively linked to educational outcomes, such as motivation and classroom engagement (Leo et al., 2023a, 2023f). Although SDT-training programs specifically aimed at for PE teachers that focus on relatedness-need supportive strategies remain scarce, the only identified study in this area has reported some positive post-intervention outcomes, especially among students (Sparks et al., 2017). Thus, by expanding on previous research through the inclusion of relatedness-thwarting behaviors and class cohesion strategies and addressing its limitations, the study expects to achieve the positive outcomes outlined above.

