### Limitations

This intervention faces certain limitations that should be considered. Firstly, although the first part of the training program can be considered brief to ensure that PE teachers effectively integrate these techniques into their PE classes, an excessively long duration could discourage their participation. Nevertheless, a booster session will be scheduled 3 months after the first two sessions of the training program. Secondly, to avoid overburdening students, we will assess their perceptions of teachers’ autonomy- and competence-supportive/thwarting behaviors with a single item to control for its effects in the analysis, which may limit our ability to fully gauge their impact. In contrast, teachers will complete the full set of items for both need-supportive and need-thwarting behaviors to control for these effects in the analysis. Thirdly, while students’ perceptions of class cohesion will be measured using a validated scale (Leo et al., 2023c), we were unable to assess class cohesion support, understood as the specific teacher behaviors aimed at promoting task cohesion (e.g., “The teacher encourages us to help each other during the development of tasks and activities) and social cohesion (e.g., “The teacher encourages us to participate together in activities outside of class.”). Fourthly, to assess the fidelity of the intervention, only two classes will be randomly observed for each experimental group teacher due to a lack of human resources. Finally, although all teachers will receive the same training program, each teacher will need to adapt the strategies to their context, the characteristics of their students, available spaces, material resources, etc. Therefore, the number and intensity of the use of relatedness supportive and class cohesion strategies may vary slightly depending on each group.

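### Hypotheses 1 and 2 are set at T2, but the planned test spans T2 and T3 and the only stated parametric follow-up is within each arm

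*Protocol article*

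**What the plan says.** Under Aim 1, the hypotheses are dated: "by Time 2 (T2), experimental group students will perceive improvements in their PE teachers’ relatedness-supportive behaviors (Hypothesis 1"). Hypothesis 2 extends this to class cohesion, relatedness satisfaction, autonomous motivation and the affective, behavioural and cognitive outcomes. The comparators are double: "compared to baseline values (Time 1 [T1]) and control group students". The Discussion repeats both for Hypothesis 1: "compared to baseline values and the control group students at post-test (T2"). For the last wave, Aim 1 says that "no specific hypotheses will be formulated regarding the intervention’s long-term effects (Time 3 [T3]) on the study variables".

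The Plan of analysis states that "between-group and within-group differences will be analyzed using repeated-measures multivariate analysis of covariance (MANCOVA"), and then specifies the model: "A 3 × 2 (Time × Condition) repeated measures MANCOVA will be performed for both teachers and students". The student covariates it names are demographic, in a list given as examples; the T1 outcome is not among them. For change in each outcome over T1, T2 and T3, the stated follow-up is that "within each group (experimental vs. control), multiple paired t-tests with Bonferroni correction will be conducted". If parametric assumptions fail, Mann–Whitney U is the between-group test, with no time point or baseline adjustment named. A longitudinal structural equation model is planned for predictive relationships.

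The measures sections on teacher interpersonal behaviour and on relatedness-supportive/thwarting behaviours, and the Limitations, add that autonomy and competence support are measured to be controlled for. The Limitations describe the students' single-item measure as included "to control for its effects in the analysis, which may limit our ability to fully gauge their impact". None of these places says which wave's value would be used.

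**The concern.** The hypotheses ask one between-arm question, at one time point. The stated test asks whether the arms' profiles differ anywhere across three waves, and the stated follow-up looks at time points inside each arm. A significant interaction therefore does not say whether the difference lies at T2, where the hypotheses are, or at T3, where there is none. The follow-up does not settle it, because a significant change in one arm and a non-significant change in the other is not a test of the difference between them.

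T1 falls at the end of the first month of school and T2 in April, so some change in both arms over the year is plausible. A reader of the eventual results could take an interaction driven by T3, or a change seen in the trained arm alone, as confirming Hypotheses 1 and 2.

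**Working it through.** The plan gives no power or effect size for a T2 contrast, so there is no figure of its own to reproduce here. The stated minimum of 385 students comes from a single-proportion formula and does not enter this point.

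**Inputs.** From the article: three waves, equal allocation, at most 10 teachers (5 per arm), at least four class groups per teacher of at least 16 students, 80% participation at T1. That gives 4 × 16 × 0.80 = 51.2, taken as 51 per teacher, and 5 × 51 = 255 per arm. Assumed: SD 1, equal correlation r between waves (0.5 unless stated), two-sided tests, one outcome at a time, independent students. Clustering by teacher would change every figure, so they show direction.

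**1. Can T3 alone drive the interaction?** Let d = (arm effect at T2, arm effect at T3). The T1-to-T2 and T1-to-T3 changes have covariance matrix S = (1 − r) × [[2, 1], [1, 2]]. The 2-df interaction test has non-centrality λ = (n/2) d′S⁻¹d.
- With d = (0, 0.3) and r = 0.5: d′S⁻¹d = 0.09 × 4/3 = 0.12, and λ = 127.5 × 0.12 = 15.3.
- Rejection probability on F(2, 507) at 0.05: about 0.95.
- A between-arm T2 contrast, on change or adjusted for T1, has a true value of zero and rejects at 0.05.
- With 192 per arm (half of 385) and r from 0.4 to 0.7, the interaction rejects with probability 0.80 to 0.98.

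**2. Does the omnibus cost power for the T2 question?** With 192 per arm, r from 0.4 to 0.7, and an effect of 0.3 SD at T2 fading to 0.15 SD at T3:

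| Test | Power |
|---|---|
| Three-wave interaction | 0.67–0.93 |
| T1-to-T2 change, between arms | 0.77–0.97 |
| T2 adjusted for T1, between arms | 0.89–0.98 |

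**3. What can the within-arm tests show?** Suppose both arms change by the same amount c, so there is no programme effect. The standard error of a within-arm change is √(2(1 − r)/n) = √(1/255) = 0.0626. The article does not give the size of the Bonferroni family; three time pairs are assumed (0.05/3, critical z = 2.394). If each arm is significant with probability p, the trained arm alone is significant with probability p(1 − p).

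| Drift c (SD) | p | Trained arm only |
|---|---|---|
| 0.05 | 0.06 | 0.05 |
| 0.10 | 0.21 | 0.17 |
| 0.15 | 0.50 | 0.25 |
| 0.20 | 0.79 | 0.17 |
| 0.25 | 0.95 | 0.05 |
| 0.30 | 0.99 | 0.01 |

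The 0.25 is the mathematical maximum of p(1 − p). If the interaction must be significant as well, simulation puts the joint event at about 0.3–2.4% across these drifts.

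**4. Precision from T1 adjustment.** The variance of the T1-adjusted contrast relative to the change-score contrast is (1 − r²) / (2(1 − r)) = (1 + r)/2, which is 0.65, 0.75 and 0.85 at r = 0.3, 0.5 and 0.7. This holds for independent students; with clustering the gain may be smaller or different.

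**The case against.** The strongest reply is that the plan does contain a between-arm test. Time × Condition is a valid test of differential change, and the paired tests are introduced only as a further look at change over time. They also answer the half of Hypotheses 1 and 2 that compares with baseline, so deleting them would leave that half untested. All of this stands. A reader might infer that the plan has no between-arm test, or that it will read significance in the trained arm alone as a programme effect. The article says neither, and if the interaction is required first, the 25% ceiling falls to about 2%, given independent students.

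It can also be said that the article is condensed, that its covariate list is open, and that Mann–Whitney U or the structural equation model could supply the missing comparison. But neither is presented as the T2 test of Hypotheses 1 and 2: the first is a fallback with no T1 adjustment or time point, and the second is for predictive relationships. Nor is the point a mere omission, since the article states a test and a follow-up that do not match its stated hypotheses.

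Two further readings go too far. Change scores are not an error under randomisation; T1 adjustment is a gain in efficiency. And a reader might infer that the plan adjusts for T2 or T3 values of autonomy and competence support, which the training could itself alter. The article names no wave, and adjustment for T1 values is consistent with its text.

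**Conclusion.** The point holds in a limited form. The hypotheses are fixed at T2 against control, while the stated test is not specific to T2 and the stated parametric follow-up cannot locate a between-arm difference there. Under the assumptions shown, a T3-only effect of 0.3 SD makes the interaction significant about 95% of the time with nothing at T2. Equal drift produces significance in the trained arm alone in about 1–25% of trials, depending on a drift that the documents do not give. That range describes a reading of the paired tests on their own; it is not the false-positive rate of the plan. The mismatch rests on the article's wording; the sizes rest on assumed correlations, effects, drifts and independent students. It should be corrected before analysis.

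**What to change.** - For each outcome under Hypotheses 1 and 2, name as the test the between-arm difference at T2, adjusted for the student's T1 score, with a 95% CI, in a model that accounts for clustering by teacher.
- Report T3 as a separate, exploratory between-arm contrast.
- Keep the within-arm paired t-tests as descriptive results for the comparison with baseline, and state that they are not evidence of a programme effect.
- If autonomy and competence support are controlled for, state that their T1 values are used.

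The cost is a change of wording in the Plan of analysis. T1 and T2 scores are already scheduled for every student, so no additional measurement is needed.

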#### Aim 2: effects of teacher program on teachers

As for the second objective, most SDT-based training programs in PE have primarily examined their effects on students (Vasconcellos et al., 2020). However, preliminary evidence also suggests that these training programs can be beneficial for teachers as well (Reeve and Cheon, 2021). Thus, using a mixed-method approach, the second aim will be to examine the effects of the training program on teachers’ beliefs, feasibility, and intention to apply relatedness-supportive and class cohesion strategies, use of relatedness-supportive behaviors, and relationship satisfaction with students. In line with this aim, it is hypothesized that, by T2, experimental group teachers will perceive improvement in beliefs, feasibility, and intention to apply relatedness-supportive and class cohesion strategies, use of relatedness-supportive behaviors, and relationship satisfaction with their students, compared to those who do not receive any training (Hypothesis 4). Due to the scarcity of prior research, we will not posit specific hypotheses about the intervention’s long-term (T3) effects on the study variables. If enough male and female teachers participate in the training program, the intervention’s effects on the study variables will also be examined by sex.

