#### Sample recruitment with inclusion criteria

Between 8–10 secondary PE teachers, assigned to the experimental group and to the control group equally, along a subset of their students, will be anticipated to take part in this study. Given the research team’s limited resources, the maximum number of participating teachers will be set at ten. Randomization will be performed using a digital tool. To minimize the risk of cross-contamination between conditions, teachers from the same high school will not participate. Teachers will be recruited through multiple channels, including social media platforms, telephone calls, and emails. Specifically, information (e.g., flyers and recruitment letters) will be shared via professional networks, PE-related social media groups, and the regional government’s official teacher registry. School principals will also be contacted directly to help disseminate the invitation within their schools.

The registration period will last approximately 2 weeks. Teachers whose participation is not approved by their school leadership will not be included. If more than 10 teachers, or multiple PE teachers from the same school, express interest, a waiting list will be created. Final selection will be based on predefined inclusion criteria and logistical feasibility, including school location, number of participants per school, schedule compatibility, and the research team’s capacity to monitor and support the intervention.

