#### Teacher training program

Experimental PE teachers will participate in a training program designed to help them provide relatedness-supportive and class cohesion strategies while avoiding relatedness-thwarting behaviors. The training will be delivered by three experienced researchers in designing and implementing motivational teacher development programs, ensuring a close trainer-to-teacher ratio (~3 trainers per 4–5 teachers) to support implementation quality and fidelity.

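### With 8–10 teachers, uncorrected partial eta squared and the 0.01/0.06/0.14 labels will often call a null teacher effect large

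*Protocol article*

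**What the plan says.** Sample recruitment with inclusion criteria sets the teacher sample: "Between 8–10 secondary PE teachers, assigned to the experimental group and to the control group equally", and "the maximum number of participating teachers will be set at ten". The training-ratio statement under Teacher training program, "3 trainers per 4–5 teachers", confirms that 8–10 is the total over both arms, so 4–5 teachers per arm.

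The Plan of analysis uses one model for both populations, crossing the three time points with the two arms: "repeated measures MANCOVA will be performed for both teachers and students". As examples of what to adjust for in the teacher model, it names five characteristics: "with covariates such as age, sex, teaching experience, type of school, and school location for teachers". The effect-size rule follows: "Effect sizes will be calculated using partial eta squared". The labels small, moderate and large are tied to values above 0.01, 0.06 and 0.14 in the sentence that begins "Effect size thresholds will be interpreted as small". It sets significance at p < 0.05 for all analyses. It states no bias correction, and it limits the labels neither to students nor to significant results.

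Hypothesis 4 (Aim 2) names five teacher outcomes: "beliefs, feasibility, and intention to apply relatedness-supportive and class cohesion strategies, use of relatedness-supportive behaviors, and relationship satisfaction with their students".

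**The concern.** Partial eta squared is the effect sum of squares divided by effect plus error sums of squares. Both parts are positive even when nothing has happened, so its expected value under no effect is above zero and grows as the error degrees of freedom shrink. Fixed cut-offs such as 0.14 take no account of this. In a large sample the bias is negligible. In a sample of 8–10 with several covariates it can be bigger than the cut-off itself.

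What is at stake is how Hypothesis 4 is read. A teacher comparison of this size will seldom be significant, so the published label may be the most visible statement about the teacher effect. A label that says large in a substantial share of null results carries little information and points in the favourable direction.

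**Working it through.** The plan gives no power, expected effect or sample size calculation for the teacher analysis, so there is no stated figure to reproduce.

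**Inputs from the Protocol article.** Total teachers N = 8 to 10; two arms; three time points; five listed teacher covariates; cut-off for large 0.14; p < 0.05; five outcomes in Hypothesis 4. The covariates are introduced as examples, so both ends of the range (none and five) are shown.

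**Assumptions.** Normal errors; one outcome at a time; sphericity for the univariate test.

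**Formulas.** Between-teacher error df: e = N − 2 − (number of covariates). Under no effect, partial eta squared follows Beta(df1/2, df2/2), with mean df1/(df1 + df2). For Time × Condition df1 = 2, which simplifies to:

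- P(> 0.14) = 0.86^(df2/2)
- value needed for p < 0.05 = 1 − 0.05^(2/df2)

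**Univariate Time × Condition, df2 = 2e**

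| N | Covariates | df2 | Null mean | P(> 0.14) | Needed for p < 0.05 |
|---|---|---|---|---|---|
| 10 | 0 | 16 | 2/18 = 0.11 | 0.86^8 = 30% | 0.31 |
| 8 | 0 | 12 | 2/14 = 0.14 | 0.86^6 = 40% | 0.39 |
| 10 | 5 | 6 | 2/8 = 0.25 | 0.86^3 = 64% | 0.63 |
| 8 | 5 | 2 | 2/4 = 0.50 | 0.86^1 = 86% | 0.95 |

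A null simulation (15,000 runs per setting) gave 29%, 41%, 63% and 86% for the four rows.

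Every significant result here also exceeds 0.14. The share of null results that are labelled large but not significant is therefore P(> 0.14) minus 5 percentage points: about 25%, 35%, 59% and 81%.

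**Multivariate (Wilks) Time × Condition, one outcome, df2 = e − 1**

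- No covariates, N = 10: df2 = 7, null mean 2/9 = 0.22, P(> 0.14) = 0.86^3.5 = 59%.
- No covariates, N = 8: df2 = 5, null mean 2/7 = 0.29, P(> 0.14) = 0.86^2.5 = 69%.
- Five covariates, N = 10: df2 = 2, null mean 0.50, P(> 0.14) = 86%.
- Five covariates, N = 8: df2 = 0, so the test cannot be computed.

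**Joint test of all five outcomes.** The multivariate Time × Condition test would need at least 10 error df. Ten teachers without covariates give 8, so only per-outcome or averaged tests are available.

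**Over the five Hypothesis 4 outcomes** (univariate test, no covariates, outcomes taken as independent): the chance of at least one null large label is 1 − 0.70^5 = 83% (N = 10) to 1 − 0.60^5 ≈ 92–93% (N = 8). Correlated outcomes would lower this.

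**Would a bias correction be enough?** Partial epsilon squared, 1 − (1 − η²)(df1 + df2)/df2, has null mean 0. Its null chance of exceeding 0.14 is still 12% (N = 10) and 16% (N = 8) without covariates, and 27% and 43% with five. It removes the bias but not the noise.

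**Students, for contrast.** With 385 students treated as independent and four covariates, the null mean is about 0.003 and P(> 0.14) is practically zero.

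**The case against.** Several points on the other side have force.

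- *The covariate set is open.* The list is illustrative, and the 64–86% figures need all five covariates entered together. This stands, and it is why the range is given. Without covariates a single univariate null effect is usually not labelled large, but 30–40% is still too often for a label meant to inform.
- *The test is not pinned down.* The plan names a multivariate analysis, while the main figures are for a univariate, one-outcome test. This is a real assumption. The multivariate one-outcome test gives higher figures, so the choice does not flatter the argument.
- *The p < 0.05 rule protects the conclusion.* It protects the claim of significance. It does not limit the label, which the plan attaches without regard to significance.
- *There is a non-parametric fallback, and Aim 2 is mixed-method.* The fallback applies only if parametric assumptions fail, which 4–5 teachers per arm can hardly show. The focus group adds qualitative evidence but does not alter the quantitative label.
- *The root cause is an overloaded teacher model.* Largely true: removing the covariates removes the worst figures. The no-covariate figures remain.

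A reader might infer more than the documents support. They do not show that noise will always be called large; this is a probability. They do not say that a non-significant but large-labelled result would count as support for Hypothesis 4. And although the same labels apply to students, no such inflation is shown there. Whether the student model handles classes and teachers properly is a separate question.

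**Conclusion.** The point holds for the teacher analysis. At the stated sample size, the stated effect-size rule will often label a null effect large: 30–40% of the time without covariates and 64–86% with all five, for a per-outcome univariate Time × Condition test under normality and sphericity. For the one-outcome multivariate test the figures are 59–69% without covariates and 86% with five at N = 10; with five at N = 8 the test is not estimable. Because the value needed for significance lies far above 0.14, many teacher results would be non-significant and yet described as large. The harm is confined to the interpretation of teacher effect sizes. It does not affect the type I error of the significance tests or the student results.

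**What to change.** For teachers only:

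1. State that the 0.01/0.06/0.14 labels will not be applied to teacher outcomes.
2. Drop the five-covariate adjustment from the teacher model.
3. For each Hypothesis 4 outcome, report the between-arm difference in T1–T2 change, in scale points, with a 95% confidence interval on N − 2 degrees of freedom (6 to 8). A small-sample-corrected standardised difference may be added. Replacing partial eta squared by a bias-corrected version while keeping the labels would not be enough.

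This point calls for no change to student reporting.

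The cost is a small change to the teacher analysis, not just to its wording: the covariates go, and a change contrast replaces the MANCOVA effect as the reported estimate. No new data are needed. Teacher effects will look less favourable, and the wide intervals will show how little 8–10 teachers can establish.
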